##### Opinions and General Knowledge of Medical Experts About a Vegan Diet and Dietary Supplements (For a Vegan Pregnancy, Infancy and Early Childhood) Should Be Established

The impact of expert opinion and knowledge on a vegan diet regarding their advice on DS for vegans (during vegan pregnancy, infancy and early childhood) should be clarified. Statistically evaluated results of the survey should allow conclusions about the influence of information supply by medical experts on nutrient supply, of vegan pregnant women and growing children (up to the age of 5 years). A possible misinterpretation of the health risk of a vegan diet during pregnancy, infancy and early childhood due to insufficient knowledge of DS could increase health risks.

A negative basic attitude towards a vegan diet influences the relationship of trust between vegans and their physicians. If there is no advice on DS, health risks can increase.

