### 2.2. Study Design

The VedieS study is an explorative, cross-sectional study. Two quantitative online surveys on a vegan diet and the intake of DS during pregnancy, infancy and early childhood (up to the age of 5 years) are carried out: The first survey focuses on vegans (parents and pregnant women) and the second survey on medical experts (pediatricians, gynecologists, general practitioners, pharmacists, dieticians). Each survey will take approximately 20–25 min to answer.

Recruitment for the survey is scheduled to take place between October 2023 and the end of July 2025. There is no survey restriction to Austria. Participants from Germany, Switzerland and Italy/South Tyrol, Liechtenstein, and Luxembourg (or other EU countries) can also answer the questionnaires and will be included in the evaluations. Since the survey is conducted in German, the survey refers to participants who understand the German language.

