### 2.5. Questionnaires

Participants are forwarded the scientific survey via a link/URL. The questionnaires can be answered at any time and from any chosen location via LimeSurvey [50] (LimeSurvey Cloud Version 6.6.7) using a tablet, PC, laptop, or smartphone. The questionnaires used in this study are provided in the Supplementary Materials. The survey tools were developed specifically for this research question and are grounded in the ideas of the Health Belief Model (HBM) and the Theory of Planned Behavior (TPB). These theoretical models served as a basis to define research questions and hypotheses and to develop questionnaire items. Two online surveys were developed: one for vegan participants (pregnant women and parents of vegan-fed children) and one for medical experts (physicians, pharmacists, and dieticians). All participants in each target group received the same version of the respective questionnaire. Within the survey for vegan participants, there are 10 question categories and corresponding detailed questions on the following: health (A), definition and reasons for a vegan diet (B), definition and understanding of and about DS (C), benefits, risks and expectations of DS (D), personal selection criteria of DS (E), level of knowledge about DS (F), sources of information about a vegan diet and DS (G), influential factors regarding a vegan diet and DS (H), deficiency and dosage of DS (I), and administration and compliance with DS intake (J). The questionnaire categories for the medical experts are structured similarly, but with a focus on topics related to patient and client counseling, as well as the personal views of physicians, pharmacists, and dietitians regarding a vegan diet and the intake of DS during pregnancy and childhood. Both questionnaires contain Likert scales, multiple-choice and single-choice questions, ranking questions, and an open-ended item. While most of the used response formats are common in surveys, the actual items were newly developed for the VedieS study. Because the questionnaires were developed based on the theoretical framework and objectives of the study itself, no standardized or pre-validated instruments were used, so no external approval was required. No additional statistical validation methods (such as factor analysis) were planned, as the questionnaires were not designed as psychometric tests but as data collection instruments based on the study hypotheses. To ensure content validity, a pre-test was conducted. The questionnaire was reviewed by nutritional experts, and a pretest was conducted with individuals from the target groups (vegans *n* = [20.0], medical experts *n* = [10.0]). This pretest focused on comprehension, relevance, and completion time of the items. Due to the received feedback, minor modifications for improvement were made. On average, completing the questionnaire took approximately 25 min for vegan participants and 20 min for medical experts.

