### 2.7. Statistical Methods and Data Analysis

The survey data will first be exported from LimeSurvey to Excel (Microsoft Corp., Redmond, WA, USA) and then analyzed using IBM SPSS Statistics version 31 (IBM Corp., Armonk, NY, USA) and R version 4.5.1 (R Core Team). Descriptive statistics will be used to summarize the results. For example, averages and standard deviations will be calculated for numeric variables, while frequencies and percentages will be reported for categorical data. Diagrams such as bar charts and boxplots will visualize the results. Depending on the type of data, different methods will be used to compare groups. Categorical variables will be analyzed using chi-square tests, and continuous variables with ANOVA. For yes/no outcomes (such as whether participants use DS or whether medical experts recommend them) logistic regression models will be applied to examine possible influencing factors. We plan to use both simple (univariate) and more complex (multivariate) logistic regression models. In the multivariate models, we will include relevant background characteristics like age, gender, education, household situation, or medical profession to better account for possible confounding effects. Since the study is exploratory, *p*-values will be reported descriptively. There will be no correction for multiple testing. Comparisons between groups will be carried out only when there is a sound theoretical reason and enough data to support it.

Possible comparisons within the vegan participant group include

-People living in rural vs. urban areas;-Supplement users vs. non-users (for themselves or their children);-Participants who changed their diet during pregnancy vs. those who did not;-Individuals who received professional advice vs. those who used informal sources like social media.

Possible comparisons within the group of medical experts include

-Those who support vs. those who reject vegan diets during pregnancy and childhood;-Those who advise supplementation vs. those who discourage it;-Differences between professions (e.g., pediatricians, pharmacists, dietitians).

Depending on the final data, additional group comparisons will be added. We will only report comparisons that are well justified and provide useful insights.

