
Research gaps concerning the administration of DS, the consistency of taking them and compliance shall be closed by statistically evaluating data from performed surveys (vegans, pediatricians, gynecologists, general practitioners, pharmacists, and dieticians). In addition, causes for the intake or rejection of DS (from a social and socio-demographic perspective) are to be examined. Resulting risks concerning the supply of nutrients are to be determined as well as the role that information sources play in this context. It is precisely these unanswered questions that underline the relevance of the VedieS study, as they are directly related to risk prevention. According to a recent study by Meulenbroeks et al. [61], pregnant women following a vegan diet often receive limited or no specific dietary guidance from obstetric healthcare providers. Only 19% of participants reported having received nutritional counseling that was specific to their needs during pregnancy. The VedieS study’s approach to identifying the cause of nutrient deficiencies during vegan pregnancy and childhood, due to a fundamental lack of information, is new and can be important for preventing health risks for vegans. Unsupplemented vegan pregnancies are associated with a higher risk of adverse outcomes [45]. These findings highlight the importance of guideline-based supplementation for vegans during sensitive life stages. The quality of the information sources used by vegans is most likely dependent on the existing attitude of the information providers. If medical experts have a negative attitude towards a vegan diet and DS, their advice may be inadequate—either due to a lack of knowledge about a purely plant-based diet, or because a vegan diet is discouraged per se without providing additional information. Knowledge gaps regarding vegan diets remain common among medical experts, likely due to limited nutrition education and a lack of familiarity with plant-based dietary patterns [44,60]. As a result of limited professional support, many vegan pregnant women turn to alternative sources of information such as books, online platforms, or peer communities to address their specific dietary needs [61]. It is important to know exactly where the information received comes from in order to be able to draw conclusions about its safety and reliability. In a cross-sectional online survey by Fuschlberger et al. [62] among Austrian vegans, 92% reported taking vitamin B_12_ through DS or fortified foods, yet fewer than 10% had consulted a medical expert. However, more research is needed to find out exactly which specific sources of information are being used.

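### The adjustment described in section 2.7 covers background characteristics only, so associations between advice and dietary supplement use or deficiency cannot carry the influence and cause conclusions the article draws from them

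*Protocol article*

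**What the plan says.** **Analysis.** Section 2.7 states that for yes/no outcomes, with DS use as a named example, "logistic regression models will be applied to examine possible influencing factors". Both univariate and multivariate models are planned. For the multivariate models, "we will include relevant background characteristics like age, gender, education, household situation, or medical profession to better account for possible confounding effects". Among the possible comparisons within the vegan group is "Individuals who received professional advice vs. those who used informal sources like social media"; no outcome is attached to it. The analyses are declared exploratory, with p-values reported descriptively.

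**Variables to be linked with responses.** Section 3.2 lists age, gender, education, urban or rural origin, household size and pregnancy status. Health status, prior deficiency and reason for seeking advice are not in that list.

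**Data collected.** Section 2.5 gives the vegan questionnaire a health category (A) and a category on deficiency and DS dosage (I). The items are in supplementary material that is not part of the text at hand.

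**Design.** Section 2.2: "The VedieS study is an explorative, cross-sectional study".

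**Intended conclusions.** Under the primary objectives (2.1.1), the objective on information sources treats the information received as acting on the choice, intake or avoidance of DS and expects its health impact to become visible. The objective on medical experts says that the results "should allow conclusions about the influence of information supply by medical experts on nutrient supply" of pregnant vegans and young children. The Discussion (section 4) describes as new the study's "approach to identifying the cause of nutrient deficiencies during vegan pregnancy and childhood, due to a fundamental lack of information".

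**Limitations.** Section 5.2 names self-report and self-selection. It does not mention confounding or the order of events.

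**The concern.** Professional advice is not handed out at random. Someone told of a low nutrient level, or worried by a symptom, has a reason to see an expert and a separate reason to take a supplement. If that happens often enough, advised respondents report more DS use even when the advice changed nothing. By the same route they report more deficiency, because the deficiency brought them to the expert. Adjusting for age, gender, education and household removes this only as far as those variables happen to predict deficiency or illness.

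Two misreadings are at stake. A higher rate of DS use among the advised could be presented as a benefit of expert information. A difference in deficiency between advice sources, in either direction, could be presented as a consequence of the information received. The stated objectives invite both readings, and the limitations section does not warn against either.

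**Working it through.** **1. Figures in the article.** The article gives no effect size, power or bias figure on this point (section 2.6.1 states that no formal power calculation was done), so there is none to reproduce. The check is an illustration. It asks what odds ratio (OR) for DS use, advised against not advised, would appear if advice had no effect and a prior deficiency or health problem U drove both.

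**2. Inputs.**
- From the studies cited in the Discussion: fewer than 10% of Austrian vegans in one survey had consulted a medical expert, and 92% of them took vitamin B12 through DS or fortified foods. In another study 19% of pregnant participants had received nutritional counseling specific to their needs.
- Assumed, not in the documents: prevalence u of U, the association of U with advice, and the association of U with DS use.

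**3. Formulas.** Let a1 and a0 be the share advised with and without U, and d1 and d0 the share using DS with and without U.
- Share advised: A = u·a1 + (1−u)·a0
- U among the advised: u·a1/A. U among the others: u·(1−a1)/(1−A)
- DS use in each group: d0 + (share with U)·(d1 − d0)
- Spurious OR = odds of DS use among the advised ÷ odds among the others

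**4. Set 1: moderate to strong associations.** Overall advice is held at 10% or 19% and DS use at 92%, u is 10–30%, and U has the same OR, 2 to 5, with advice and with DS use.

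Worked case (advice 19%, u = 20%, both ORs 3): a0 = 15.1%, a1 = 34.7%, d0 = 90.8%, d1 = 96.7%. U among the advised is 0.20 × 0.347/0.19 = 36.6%, and among the others 0.20 × 0.653/0.81 = 16.1%. DS use is 93.0% against 91.8%, OR 1.19.

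| OR of U with advice and with DS use | Spurious OR, advice → DS |
|---|---|
| 2 | 1.04–1.10 |
| 3 | 1.10–1.27 |
| 5 | 1.20–1.64 |
| 1 with advice, 3 with DS use | 1.00 |

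With 1000 respondents, the chance of a two-sided p < 0.05 in the direction of the bias is 0.03 to 0.26 in the first three rows (0.025 with no bias). With DS use assumed at 80% and advice at 19% or 50%, the ORs are 1.04–1.64 and that chance reaches 0.66.

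**5. Set 2: very strong associations.** Advice 40–60% with U and 10% without; DS use 98–99% with U and 91% without; u = 10–15%.
- Weakest corner (u = 10%, 40%, 98%): U is 0.04/0.13 = 30.8% of the advised and 0.06/0.87 = 6.9% of the others. DS use is 93.2% against 91.5%, OR 1.27.
- Strongest corner (u = 15%, 60%, 99%): U is 0.09/0.175 = 51.4% and 0.06/0.825 = 7.3%. DS use is 95.1% against 91.6%, OR 1.79.

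The last case needs U to have an OR of 13.5 with advice (60% against 10%) and 9.8 with DS use (99% against 91%).

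**6. Deficiency by advice source.** Nothing can be derived here. If deficiency comes first, the OR between advice and deficiency simply equals the assumed OR for seeking advice: 2 to 5 in set 1, and 6.0 (40% against 10%) or 13.5 in set 2. It is an input, not an estimate of bias.

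**7. After adjustment.** With U in the model the advice-DS OR is 1.00 in every case, by construction, because these scenarios let U come before advice. A cross-sectional survey does not guarantee that order.

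**The case against.** **The covariate list is open.** The examples in section 2.7 are introduced as illustrations, and a fuller protocol or analysis plan may name more covariates. A reader might infer that adjustment is restricted to demographics. The text does not say that, and an incomplete list in an article would be no finding. What stands is narrower: the article itself describes the class of covariates as background characteristics, gives only demographic and professional examples, and states influence and cause conclusions that this class cannot support.

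**No advice-deficiency analysis is specified.** This is correct. Section 2.7 attaches no outcome to the advice comparison and does not name deficiency as an outcome. The link appears only in the objectives and the Discussion, so the point there concerns interpretation.

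**The bias is assumed, and so is its direction.** A reader might infer that the comparisons are in fact confounded, and that the advised group will show more DS use and more deficiency. The documents do not support that. They report other routes: parents avoid telling pediatricians about the diet for fear of criticism, and vegans turn to peers when experts seem negative. These could offset or reverse the pattern. If health problems do not drive advice-seeking, the bias from this source is nil.

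**The study is exploratory.** Descriptive p-values moderate claims of significance. They do not remove bias from an odds ratio, nor do they cover wording about cause.

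**Adjustment may itself mislead.** Reported deficiency may follow advice, through testing and diagnosis, or result from not taking DS. Conditioning on it could then remove a real association or add bias. This stands, and it rules out making the adjusted or deficiency-free result the main reading.

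**Conclusion.** The concern holds as a mismatch between the adjustment described and the conclusions intended. With one cross-sectional survey and adjustment described through background characteristics, the advice-DS contrast and any reading of deficiency by advice source are open to confounding by indication and reverse order. The article does not acknowledge this.

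Direction and size are unknown from the documents. With no true effect of advice, the spurious OR for DS use is about 1.0 to 1.8. It stays within 1.04 to 1.27 when the assumed associations are moderate (ORs of 2 to 3, advice 10% or 19%, DS use 92%), and reaches 1.79 only under very strong ones. All of this rests on assumed prevalences and associations. For deficiency no size can be derived.

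The primary outcomes, which section 3.1 bases on response frequencies, are not affected as descriptions. The planned explanation of them is.

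**What to change.** 1. In section 2.7, where the items in categories A and I allow, report the advice-DS contrast both without and with reported deficiency or health problem as a covariate or stratum. Place the two side by side and fix neither as the main reading.
2. Report deficiency by advice source as an association with no direction of effect, unless the questionnaire records which came first.
3. Replace the influence wording in the medical-expert objective of section 2.1.1, and the cause wording in the Discussion, with association.
4. Add confounding, including the reason for seeking advice, and temporal order to the limitations in section 5.2.

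**Cost.** One extra covariate, one extra table and some changes of wording; no new data if the items are suitable. Where advice led to the diagnosis, the adjusted figure may remove part of a real association, which is why both figures should be shown. If the items do not allow the adjustment, steps 2 to 4 still apply.

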Secondary outcome measures for medical experts include gathering the personal opinions of physicians, pharmacists, and dietitians regarding DS and a vegan diet during pregnancy and childhood. This encompasses assessing the perceived health impacts of a vegan diet in these life stages. Furthermore, the study evaluates compliance with supplement intake among vegans, the resulting implications, and any challenges in administering DS to their children. Experts’ experiences with advising vegan diets and their stance on recommending or discouraging the use of DS should be assessed as well.

A statistical analysis on the survey data will be conducted to identify and interpret any previously unrecognized relationships between responses and potential consequences for vegans.

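### Section 2.7 lets comparisons be added on the final data and reports only those judged useful, so the reported associations are liable to be a selected subset with an unknown denominator

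*Protocol article*

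**What the plan says.** Section 2.7 of the protocol article sets out the group comparisons. The study is declared exploratory, p-"values will be reported descriptively", and "There will be no correction for multiple testing". One condition governs what is done: "Comparisons between groups will be carried out only when there is a sound theoretical reason and enough data to support it".

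Two lists follow, each introduced as possible rather than fixed ("Possible comparisons within the vegan participant group include" and a parallel line for the experts). They hold four comparisons among vegan participants and three among medical experts. The section then closes with two sentences, of which the first opens the list and the second sets a reporting rule: "Depending on the final data, additional group comparisons will be added. We will only report comparisons that are well justified and provide useful insights".

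Section 3.2 adds that the survey data will be analysed "to identify and interpret any previously unrecognized relationships between responses and potential consequences for vegans".

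**The concern.** The closing sentences of Section 2.7 state a rule, so this is not a matter of detail left out. The rule has two parts. The set of comparisons may grow once the final data are in hand, and of the comparisons made only some will be reported. A comparison can be judged well justified in advance. Whether it provides useful insight is naturally judged after its result is known.

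Two things are at stake. First, if striking results pass the filter more easily than flat ones, the published differences are on average too large. Second, an unadjusted p-value offered as description can be weighed only by a reader who knows how many comparisons were examined, and this rule does not disclose that number. Because even the seven listed comparisons are only possible ones, a listed comparison missing from the report cannot be told apart from one that was never run.

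The associations are meant to influence counselling. Section 2.1 says the study is intended to show how much depends on professional advice. Against that aim, a flat comparison of professional advice with informal sources could easily be thought uninformative, although it bears directly on the study's hypotheses.

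**Working it through.** **1. What each sentence of Section 2.7 controls**

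- Theoretical reason and enough data: controls which comparisons are carried out. Neither term has a criterion.
- Additions depending on the final data: leaves the number and content of comparisons open.
- Well justified and useful: controls which comparisons are reported. Neither term has a criterion.

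The first condition does not make the third harmless. If everything carried out were to be reported, the last sentence would have no work to do.

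**2. The plan's own figures**

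The article states no alpha, power or error rate (Section 2.6.1 says no formal power calculation was made), so there is no error figure to reproduce. Only the sample sizes enter below: 1000 vegan participants and about 60 per expert group (Section 2.6.1). The 1000 follows from 400,000 × 1% × 25% = 1000; nothing here depends on that derivation.

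**3. Size of the selection effect (illustration)**

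Assumptions: useful is taken to mean p<0.05 two-sided, the outcome is yes/no, the reference proportion is 50%, and the test is a pooled two-proportion z-test. The 500/500 and 100/900 splits of 1000 are also assumed.

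The smallest observed difference that can pass is about 1.96 × √[0.25 × (1/n₁ + 1/n₂)]:

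- 60 vs 60: 1.96 × √(0.25 × 2/60) = 17.9 points
- 100 vs 900: 1.96 × √[0.25 × (1/100 + 1/900)] = 10.3 points
- 500 vs 500: 1.96 × √(0.25 × 2/500) = 6.2 points

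A true difference below the threshold can pass only by being overestimated. Simulation with 400,000 runs per row gives:

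| Groups | True difference (points) | Share passing | Mean absolute difference, all runs | Mean absolute difference, passing runs |
|---|---|---|---|---|
| 60 vs 60 | 0 | 5.5% | 7.3 | 21.0 |
| 60 vs 60 | 10 | 20.5% | 11.2 | 22.6 |
| 60 vs 60 | 20 | 61.9% | 20.1 | 25.4 |
| 100 vs 900 | 5 | 15.9% | 6.0 | 13.0 |
| 100 vs 900 | 10 | 48.1% | 10.1 | 14.3 |
| 500 vs 500 | 5 | 36.4% | 5.2 | 8.3 |
| 500 vs 500 | 10 | 89.3% | 10.0 | 10.6 |

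The inflation is large for groups of the planned expert size and for unequal splits. It is small for a large balanced split with a real effect.

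**4. The missing denominator (illustration)**

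Inputs: 4 listed vegan comparisons (Section 2.7) and 10 question categories (Section 2.5). Assumptions: one item per category, all nulls true, independent tests, alpha 5%.

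- Tests: 4 × 10 = 40
- Expected chance findings: 40 × 0.05 = 2.0
- Chance of at least one: 1 − 0.95⁴⁰ = 0.87
- At an assumed alpha of 1%: 40 × 0.01 = 0.4 expected, and 1 − 0.99⁴⁰ = 0.33

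These values would be the same if every test were reported, so they do not measure selection bias. They show what a reader would have to weigh the findings against, which is possible only if the count is disclosed.

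**The case against.** The strongest reply has five parts.

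- **The wording does not say that results drive the choice.** Additions that depend on the final data may mean achieved subgroup sizes, which is plausible in a hard-to-reach population with uncertain expert participation (Section 2.6.1). Usefulness is not tied to significance, and a finding of no rural/urban difference could well be reported as useful. This stands. A reader might infer that null comparisons will be suppressed and that the reported effects will certainly be inflated. The text permits that outcome but does not state it, so liable to be is as far as the document goes.
- **Unadjusted p-values are legitimate here.** A reader might infer that the absence of a multiplicity correction is the fault. In a declared exploratory survey with descriptive p-values and no hypothesis-testing design, it is not. The search for unrecognised relationships in Section 3.2 is likewise an exploratory aim and not a second instance of selective reporting, though it fits awkwardly with a condition that every comparison needs a theoretical reason.
- **The main results are elsewhere.** Section 3.1 bases the findings on frequency and prevalence of responses. Which group comparisons are reported hardly touches those. This stands too, and limits the reach of the point.
- **There is a safeguard.** The theoretical-reason condition is real, but it acts on what is run. It leaves the reporting filter in place.
- **A fuller plan may exist.** A complete comparison list could properly sit in an analysis plan that is not shown, and its absence from the article is no fault. The reporting rule, however, is stated in the article itself, and a longer list elsewhere would not undo it.

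**Conclusion.** The point holds in limited form. Followed as written, Section 2.7 allows comparisons to be run and left unreported on a judgement that is most naturally made after seeing the result, and it does not disclose how many were examined. The reported group associations are therefore liable to be a selected subset with effect sizes biased away from zero, mainly for small or unequal groups such as the expert groups of about 60, and the descriptive p-values lack a known denominator.

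The sizes shown are illustrations. A 10-point difference becoming 22.6 at 60 vs 60, or 10.6 at 500 vs 500, assumes that useful means p<0.05. The 2.0 expected chance findings assume alpha 5%, independence, all nulls true and one item per category. The document fixes none of these. The defect itself rests on the stated rule and not on these figures.

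**What to change.** Replace the last two sentences of Section 2.7 with:

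> All group comparisons performed will be reported, in a supplement if needed, with effect estimates, 95% confidence intervals and the total number examined; comparisons listed here are labelled pre-specified and any added after data review are labelled post hoc.

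This keeps the exploratory design and the freedom to add comparisons, and needs no new data. Benjamini-Hochberg adjusted p-values beside the raw ones are optional; the essential step is full disclosure. A log of comparisons kept from the start of analysis makes the total easy to state.

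The cost is one supplementary table, and some associations will look less striking.
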